#### Control intervention

Participants in the control group will receive standard treatment with casework at the participating hospitals. Also, participants in the control group will receive a pamphlet on suicide prevention following the psychoeducation program and during their visits for periodic evaluations 6 months after enrollment and every year thereafter.

### Evaluations

#### Psychiatric Evaluations

Evaluators including psychiatrists, clinical psychologists, psychiatric social workers, and/or other mental health professionals, will conduct the psychiatric evaluations. In order to conduct blinded evaluations, evaluators will not know the participants' assigned groups, status of implementation of the intervention, or information on events obtained by other on-site research staff. Moreover, to achieve blinded evaluations, evaluators will not serve as case managers or practitioners in charge of the *Psychoeducation Program II*.

These evaluators will conduct psychiatric evaluations of all participants enrolled at the hospitals and will use a case sheet at 6 months from the date written consent was obtained and every year thereafter until the completion of the study. Evaluations can be carried out up to 1 month before or after the scheduled date.

Evaluations generally will take place as face-to-face interviews at the participating hospitals. The evaluators will notify the participants of the interview schedules 7 days before the scheduled dates via e-mail or regular mail. E-mail messages will be prepared with the e-mail form on the input system and sent via the dedicated e-mail address for this study; the dedicated email address does not permit any replies. Regular mail will be sent by the participating hospitals, and words such as suicide will not be printed on the envelopes. The evaluators will schedule the next evaluation date and inform participants at the end of each interview.

Evaluations will include the following:

1) Participant survival (or cause of death noted in the case of death of the participant)

2) Whether or not suicidal behavior has been repeated

3) Any events other than (1) or (2)

4) Stress factors

5) Persons and/or organizations to consult

6) Treatment status (outpatient or inpatient)

7) Physical function

8) Drinking habits

9) Evaluations using scales

a) Beck Hopelessness Scale [21]

b) Beck Depression Inventory-II (BDI-II) [22]

c) SF-36 [23]

#### Events

Events will be classified as follows:

1) Recurrent suicidal behavior

2) Total deaths (from any cause)

3) Self-harm

4) Adverse events other than (1), (2), or (3): Any unfavorable and unintended occurrence in a participant, whether or not there is a causal relationship with the intervention, will be recorded.

When identifying an event, the on-site research staff at the participating hospital will record the information according to the event review sheet and will confirm the information with the investigator. If there are no complications, the on-site research staff will enter the content of the event into the web input system. If necessary, on-site research staff will consult with the on-site research coordinator and the study group management office regarding any aspects of the event that are unclear. The on-site research coordinator will notify the hospital director about any serious adverse event and will fax the event review sheet directly to the study group management office.

The data center will consolidate the input data and periodically provide data to the study group management office and the chairperson of the event review committee, according to data management procedures. The study group management office and the chairperson of the event review committee should hold monthly event review meetings to evaluate and assess details of events based on the material provided.

Specific aspects of events will be described in the event definitions and event review procedures.

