#### Case management intervention in the experimental group

Case managers will periodically contact participants assigned to the experimental intervention group (on the 1^st^, 4^th^, 8^th^, and 12^th ^week and the 6^th ^month after the day of written consent, and every 6 months thereafter until the end of the study). Case managers will inform participants about the date of their scheduled interviews in advance, via e-mail or regular mail. E-mail messages for participants will be prepared with the e-mail form on the input system and sent via the dedicated e-mail address for this study; the dedicated e-mail address does not permit any replies. Regular mail will be sent by participating hospitals, and words such as suicide will not be printed on the envelopes.

In principle, case management should be accomplished through direct dialogue (face-to-face interviews), where a telephone conversation is the next best option. Interviews should be conducted at participating hospitals. If case managers cannot reach participants, case managers will approach participant family members who have given their consent to be contacted in advance.

The interview scheduled for the first week should be conducted within two days before or after the scheduled date. Interviews for the 4^th^, 8^th^, and 12^th ^weeks should be conducted within a week, for the 6^th ^month within 2 weeks, and thereafter within 1 month before or after the scheduled date.

Case management will include the following activities:

1) Periodic interviews (either face-to-face or via telephone) with participants

2) Collection of information about each participant's background and treatment status

3) Encouragement of psychiatric treatment to the participants

4) Coordination of appointments with psychiatrists and primary care physicians

5) Encouragement of psychiatric treatment to the participants who have stopped receiving the treatment

6) Referrals to social resources and private support organizations and coordination for utilization of these resources

7) Providing information to participants and the *Psychoeducation Program II *to their family members during hospitalization

8) Providing Internet-based information (website only for the experimental intervention group)

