Case managers will conduct periodic case conferences with psychiatrists. The study group management office and the intervention program committee will periodically hold case conference meetings with the study group, visit the participating hospitals, and meet with case managers, as necessary.

Regarding Internet-based information, participants in the experimental intervention group who access the website will receive information about the psychoeducation program, support organizations, and a self-diagnosis program. The dedicated intervention website will contain pages providing an introduction to social resources and serial articles, applied intervention (including psychoeducation and self-evaluation tools), and crisis intervention. The Intervention Program Committee will periodically update the content and articles on the website.

Standard treatment will be provided to subjects in the experimental group at each participating hospital. In addition, each participant in the experimental group will receive a pamphlet on suicide prevention following the psychoeducation program and at hospital visits after enrollment.

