### Evaluation of events

The event review committee will assess events related to the primary and secondary outcomes, while the assignment of the participants remains blinded. The event review committee will specify the evaluation criterion in the event definitions and event review procedures.

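### The study group management office shares in evaluating events yet can learn allocation through its case-management work, so the stated blinding of event assessment is not secured

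*Protocol article*

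**What the plan says.** The trial is open-label (Methods/Design). The Organization section lists the study group management office and the event review committee as separate bodies.

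Two sections describe the assessment of events:

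- Evaluation of events: "The event review committee will assess events related to the primary and secondary outcomes, while the assignment of the participants remains blinded".
- Events: the "study group management office and the chairperson of the event review committee should hold monthly event review meetings to evaluate and assess" event details. The data center is to "periodically provide data to the study group management office and the chairperson of the event review committee, according to data management procedures".

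The management office has other contacts with sites:

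- With the intervention program committee, it holds periodic case conferences with the study group, and the two will "visit the participating hospitals, and meet with case managers, as necessary" (Case management intervention in the experimental group). The same section says that "Case managers will periodically contact participants assigned to the experimental intervention group". The task schedule (Table 1) marks case management as given in that group only.
- If necessary, site staff "will consult with the on-site research coordinator and the study group management office regarding any aspects of the event that are unclear" (Events).
- For a serious adverse event, the site coordinator "will fax the event review sheet directly to the study group management office" (Events).

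The Events section lists recurrent suicidal behavior and self-harm as separate classes. The first recurrent suicidal behavior is the primary outcome. The number of self-harm behaviors is a secondary outcome.

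**The concern.** In an open trial, blinded event assessment is the main protection for an endpoint that involves judgement. Here a body outside the committee takes part in evaluating events, and its other duties bring it into contact with the staff who deliver the experimental intervention. A participant discussed as a case-management case is an experimental-arm participant.

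The decision at risk is whether an act counts as recurrent suicidal behavior, and so towards the primary outcome, or as self-harm, which does not. The article does not say how the two are separated, but the distinction plausibly rests on a judgement of intent. The events that sites find unclear are the most open to such judgement, and those are the ones on which the office may be consulted. If knowledge of the arm shifted that line even slightly, the primary comparison would shift with it.

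**Working it through.** **Comparing the sections**

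1. *Does the office take part in evaluation?* Yes. The Events section names it with the committee chairperson as holding the monthly meetings.
2. *Is the office part of the committee?* No. The Organization section lists them separately.
3. *Can the office learn allocation?* Yes, by at least one route. Case managers work only in the experimental arm, and the office joins case conferences and meets them. Queries from open-label sites are a second possible route.
4. *Would masked event sheets close these routes?* Not fully. Masking removes what is on the sheet, but not what the office has learned in case conferences, visits or queries.
5. *Is a separation stated elsewhere?* Yes, for the psychiatric evaluators. They may not act as case managers and are kept unaware of group and of events obtained by other staff. No such separation is stated for the office.

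None of this depends on a figure in the protocol, so there is no plan figure to reproduce.

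**Illustration of what a tilt would cost**

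Inputs from the protocol article: 421 participants per group; 15% annual incidence in the control group; 3.5 years of enrollment and 1.5 years of follow-up after it; one-sided level 2.5%.

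Assumptions: true hazard ratio 1; uniform enrollment; exponential times; no loss to follow-up; no interim looks; a fraction m of experimental-arm attempts relabelled as self-harm, none in control, and none corrected later.

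- Hazard: λ = −ln(1 − 0.15) = 0.1625 per year.
- Event probability with follow-up spread evenly from 1.5 to 5 years: P(λ) = 1 − [exp(−1.5λ) − exp(−5λ)] / (3.5λ).
- Control: P(0.1625) = 0.4023, so 421 × 0.4023 = 169.4 events.
- The experimental arm's apparent hazard is 0.1625 × (1 − m), so the apparent hazard ratio is 1 − m.
- Rejection probability: Φ( (√d / 2) × [−ln(1 − m)] − 1.96 ), where d is the total number of counted events.

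| m | Apparent HR | Experimental events | d | Shift in z | One-sided type I error |
|---|---|---|---|---|---|
| 0 | 1.00 | 169.4 | 339 | 0 | 2.5% |
| 2% | 0.98 | 166.9 | 336 | 0.185 | 3.8% |
| 5% | 0.95 | 163.0 | 332 | 0.468 | 6.8% |
| 10% | 0.90 | 156.4 | 326 | 0.951 | 15.6% |

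If 15% is read as a hazard rather than an annual risk, the last three rows become 3.8%, 6.6% and 15.0%.

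**The case against.** The strongest reply is that the two sections do not strictly contradict each other. The monthly meeting includes the committee chairperson, uses material supplied by the data center, and may only prepare for a blinded decision by the committee. The article does not say that the meeting makes the final classification. This stands, and it rules out the stronger reading that a reader might infer, namely that the primary endpoint is not adjudicated blind.

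Other tempting readings also fail:

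- *The site reports are unblinded.* Nothing says that the event sheet shows the assigned group, and direct faxing is described only for serious adverse events.
- *Those who run the intervention sit in the review meeting.* Neither the intervention program committee nor the case managers are named there. What is stated is that the office joins that committee in overseeing case management.

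It is also fair to say that masking rules may sit in the event definitions and event review procedures, which are not shown, and that the periodic monitoring reports sent to the office give events by blinded group. But the point concerns a role that the article does state, not a missing detail. Masked reports, whether aggregate or individual, do not undo what the office learns from case managers.

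Finally, the relabelling rates are assumed, and the same arithmetic would fit any open trial with these rates and this size. It also treats every primary event as open to relabelling, although completed suicides are among them. The figures therefore show sensitivity to a tilt. They do not estimate one.

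**Conclusion.** The point holds in this limited form: the Events section gives a part in event evaluation to an office that can learn allocation, so the blinding stated under evaluation of events is not secured by the process described. The documents do not show that assessment is in fact unblinded, nor that any misclassification would occur.

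No size can be derived from the documents. Under assumed relabelling of 5% or 10% in the experimental arm only, with no true effect and no later correction, one-sided type I error would be about 6.8% or 16% against the nominal 2.5%. That the distinction between attempt and self-harm rests on judgement is itself an inference, since the event definitions are not shown. This is a should-fix point: a cheap improvement, not a flaw that invalidates the design.

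**What to change.** Reconcile the two sections as follows:

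- Limit the management office to administrative handling of event reports.
- State that only the event review committee classifies events, covering all suspected attempts and all self-harm reports. Self-harm is already a secondary outcome within the committee's remit, so this mainly makes the rule explicit.
- Have the data center send the committee material with allocation cues removed, such as case-manager contacts, use of the intervention website and the contact schedule.
- Route site queries on unclear events to the committee through the data center. Serious adverse event reports can still go to the office for safety purposes.
- Pre-specify one sensitivity analysis: time to first recurrent suicidal behavior or self-harm, whichever comes first. Relabelling between these two classes cannot move it. The protocol already allows sensitivity analyses as necessary, so this names one of them.

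The cost is a procedural amendment using existing bodies, some redaction work and one extra analysis. The combined endpoint may dilute a true effect on suicide attempts and does not protect against events being placed outside both classes. It should therefore support the primary analysis, not replace it.

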### Time periods during the study

Study period: August 2005 through March 2011

Enrollment period: July 2006 through December 2009

Follow-up period: July 2006 through June 2011

### Preconditions for hospital participation in the study

A hospital satisfying the following preconditions may participate in the study: The hospital should have both emergency medicine and psychiatry departments and an established collaborative agreement between those departments, so that the hospital can provide patients with psychiatric interventions to the emergency department.

Within the enrollment period, the hospital can recruit and obtain consent from at least 20 patients who are eligible to participate in the context of inclusion and exclusion criteria. The hospital will perform follow-up on the patients until study completion.

All participating researchers should take a seminar on suicide prevention (epidemiology, risk factors, psychology, prevention, intervention, and postvention). According to their respective roles, each participating researcher may take other seminars on psychiatric diagnosis (Mini International Neuropsychiatric Interview [M.I.N.I.; [24]]), the psychoeducation program, psychiatric evaluation, and assessment by scales (Suicide Intent Scale [18], Beck Hopelessness Scale [21], BDI-II [22], and SF-36 [23]).

### Approval of the study protocol

The study protocol will be reviewed and approved by the Central Research Ethics Committee. In principle, the study protocol also will have to be reviewed and approved by the On-site Research Ethics Committee at each participating hospital.

### Data collection

Data collection listed will be conducted according to the appropriate timing and each aspect of the relevant information.

#### Data collected at time of enrollment

1) Basic information on the participant

Initials, ID number, age, gender, other people living with the participant, marital status, education, employment, and other information

2) Information about suicidal behavior

Date and time, means, motivation, Beck Suicide Ideation Scale, and other details of past suicidal behavior

3) Demographic status (items marked with an asterisk on the forms are allocation adjustment factors): Age, gender, history of suicide attempts, DSM-IV diagnosis with M.I.N.I. [24], history of psychiatric treatment, history of hospital visits for physical problems, drinking habits, family history, and individuals to consult

4) Condition (psychiatric and physical diagnoses) at the time of enrollment

a) Suicide Intent Scale (only at the time of enrollment) [18]

b) Beck Hopelessness Scale [21]

c) BDI-II [22]

d) SF-36 [23]

#### Data collected at time of discharge

1) Date of hospital discharge

2) Discharge plans

#### Data collected during case management

1) Psychological and social conditions

2) Status of treatment for psychiatric and/or physical problems

3) Utilization of social resources

4) Utilization of dedicated intervention website

5) Degree of participant satisfaction with case management

#### Data collected during psychiatric evaluations

1) Participant survival (or cause of death of the participant)

2) Whether or not a suicidal behavior has been repeated

3) Any events other than (1) or (2)

4) Stress factors

5) Individuals and/or organizations to consult

6) Other medical services received (during clinical visits and/or hospital admission)

7) Physical function

8) Drinking habits

9) Evaluations using scales

a) Beck Hopelessness Scale [21]

b) BDI-II [22]

c) SF-36 [23]

### Outcomes

#### Primary outcome

The incidence of first recurrent suicidal behavior (expressed as attempted or completed suicides/person-year) will be used as the primary outcome, because an individual who reattempts suicide is at high risk for completion of suicide. Therefore, in order to develop effective suicide prevention strategies, it is essential to measure the time to the next suicidal behavior.

#### Secondary outcomes

Secondary outcomes will include the following:

1) Mortality rate (for any cause of death/person-year) during the study period2) The number and incidence rate of recurrent suicidal behavior, expressed as repeated suicidal attempts/person-year

3) The number of self-harm behaviors

4) Types and numbers of individuals and/or organizations to consult

5) Other medical services received (during clinical visits and/or hospital admission)

6) Physical function

7) Beck Hopelessness Scale score

8) BDI-II score

9) SF-36 score

### Evaluation of events

The event review committee will assess events related to the primary and secondary outcomes, while the assignment of the participants remains blinded. The event review committee will specify the evaluation criterion in the event definitions and event review procedures.

### Safety management

The on-site research staff at the participating hospitals will take necessary and appropriate actions to ensure the safety of participants when a serious adverse event occurs or a participant is at impending risk of suicide during the study. The on-site research staff will contact the on-site research coordinator at the hospital, and the coordinator will submit a report promptly to the director of the hospital and the study group management office.

### Statistical analyses

#### Primary analysis

The primary objective of this study is to examine whether or not the period of time until recurrent suicidal behavior (either attempt or completion of suicide) of participants in the experimental intervention group is significantly different from that of the control group. The stratified log-rank test based on allocation factors will be performed for all eligible participants in the intent-to-treat analysis, in order to examine the null hypothesis that the two groups are equal in the period of time until the incidence of the event.

A one-sided test will be conducted, because there would be no interest in the case that the experimental intervention is found to be significantly inferior to standard treatment. In this case, the level of significance will be set at 2.5% for the one-sided test, and the power will be set at 90%.

Sensitivity analyses will be performed as necessary, and a regression analysis will be performed with risk factors of potential influence.

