### Organization

JMHLW selected the Japan Foundation for Neuroscience and Mental Health (JFNMH) as the primary institution responsible for J-MISP, in close collaboration with the National Center of Neurology and Psychiatry. The J-MISP administration office in JFNMH will organize overall administrative procedures regarding the operations of the ACTION-J study group. The office will also establish and operate the steering committee, central research ethics committee, study evaluation committee, and study progress control committee.

The ACTION-J study group will include 19 participating hospitals in Japan. The study group will comprise the following: the study group management office, each participating hospital, the steering committee, the principal statistician, the independent statistician, the intervention program committee, the event review committee, and the data management center for technical support.

Each participating hospital will have psychiatrists, emergency department physicians, case managers, and other personnel. In addition, one coordinator, either a psychiatrist or an emergency physician, will be assigned to each participating hospital. Other participating researchers in this study include experts in suicide prevention, nurses, clinical psychologists, psychiatric social workers, biostatisticians, epidemiologists, and coordinators of the data management center.

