### Estimation of sample size

The total sample size is 842 participants, including 421 participants in each of the two treatment groups. Calculation of the desired sample size was based on the following rationale. According to a study of suicidal individuals transported to psychiatric emergency facilities in Japan, the annual incidence rate of events (including death) was set at 15% in the control group [19]. The target reduction in recurrent suicidal behavior in the trial intervention group was set at approximately 30%; the annual incidence rate of events (including death) in the intervention group was estimated to be 10.5% [20].

Based on this estimation, we calculated the sample size using the method of Shoenfeld and Richter, in order to confirm that the intervention group is superior, with a significance level of 2.5% for the one-sided test and a power of 90%, dependent on a 3.5-year-enrollment period and a 1.5-year follow-up period after enrollment. Given these assumptions, the desired number of participants per group was calculated to be 518, and number of events was expected to be 296. Sample size was set to increase the likelihood that the expected number of events (≥ 90% if no participant is lost to follow-up) would be observed during the study period.

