### Randomization

Using the minimization method, participants will be randomly assigned to either the intervention group or control group. Central assignment involving an Internet-based assignment system will be performed.

Participants will be randomly assigned to one of the two groups according to the following factors:

1) Hospital

2) Gender

3) Age (< 40 or ≥ 40 years)

4) History of suicide attempts

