#### Interim analyses

Interim analyses will be performed to evaluate achievement of the primary objective of the study. The analyses will be conducted twice during the study. Participant recruitment will be continued during the interim analyses.

For the interim analysis, the Lan-DeMets spending function will be used to adjust for multiplicity and to maintain the alpha error of the overall study at 2.5% for the one-sided test. The difference between the two groups in the period up to the event occurrence, using the O'Brien-Fleming alpha-spending function, will be examined for statistical significance.

The study will be terminated if the period up to the event occurrence in the trial intervention group exceeds that of the control group and the *p*-value of the log-rank sum test is less than the significance level defined by the method described above.

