#### Secondary analysis

Secondary outcomes will be examined in order to reinforce the findings of the primary analysis. For analysis of secondary outcomes, the period up to event occurrence will be analyzed with the stratified log-rank test. Subgroup analysis of the primary and secondary outcomes will be performed by hospital, gender, age (< 40 or ≥ 40 years), and occurrence of suicide attempt before enrollment in this study. Because of the exploratory nature of the secondary analysis, no adjustment for multiplicity will be made.

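### Read plainly, the primary log-rank test is stratified into 152 cells for 842 participants, which gives about 78–83% power rather than the stated 90%

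*Protocol article*

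**What the plan says.** All references are to the protocol article.

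- **Statistical analyses, Primary analysis:** "The stratified log-rank test based on allocation factors will be performed for all eligible participants in the intent-to-treat analysis". The same section sets a one-sided 2.5% level and repeats a power of 90%.
- **Randomization:** minimization is used. "Participants will be randomly assigned to one of the two groups according to the following factors": hospital, gender, age split at 40, and history of suicide attempts. The number of levels for history is not given, but Secondary analysis describes the matching subgroup factor as "occurrence of suicide attempt before enrollment in this study", which suggests yes/no.
- **Organization:** "The ACTION-J study group will include 19 participating hospitals in Japan".
- **Estimation of sample size:** "The total sample size is 842 participants, including 421 participants in each of the two treatment groups". Also, "the annual incidence rate of events (including death) was set at 15% in the control group", against 10.5% with the intervention. Enrollment lasts 3.5 years with 1.5 further years of follow-up, and 296 events are expected. The same section also gives a calculated 518 per group, which conflicts with 421.
- **Interim analyses:** the stopping rule requires that the p-value of the "log-rank sum test is less than the significance level" set by the spending function. The word stratified does not appear there.

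The article does not drop a factor, select a subset or pool small strata.

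**The concern.** A stratified log-rank test compares arms only within a stratum. An event adds to the test in proportion to p(1 − p), where p is the share of the stratum's risk set in the intervention arm. If only one arm is still at risk, that product is zero.

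Minimization balances the margins of the four factors, not their cross-classification, so within a small cell the split between arms is close to a coin toss. For a risk set of n people the expected p(1 − p) is then ¼ × (1 − 1/n), against ¼ in a large balanced set. A risk set of 5 keeps 80% of the information, one of 2 keeps 50%, and one of 1 keeps none. Cells that start at about 5.5 people and shrink over follow-up fall in this range.

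The sample size makes no visible allowance for this. The power printed beside the primary test may therefore not be the power of that test. At stake is a higher chance of missing the target effect in a trial of up to five years.

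**Working it through.** **1. Reproduce the stated design.** Annual risks of 15% and 10.5% convert to exponential hazards −ln(0.85) = 0.1625 and −ln(0.895) = 0.1109, so HR = 0.6826.

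- Freedman: events = ((1 + HR)/(1 − HR))² × (1.960 + 1.282)² = (1.6826/0.3174)² × 10.51, giving 296 after rounding up. This matches the plan exactly.
- Schoenfeld: 4 × 10.51/(ln 0.6826)² gives 289.
- With uniform accrual over 3.5 years and closure at 5 years, P(event) = 1 − (e^(−1.5λ) − e^(−5λ))/(3.5λ). This is 0.402 for control and 0.298 for intervention, mean 0.350.
- N = 296/0.3503 = 845, against 842 stated. At 842, about 295 events are expected.

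So 842, 296 events and 90% power belong together, under an ordinary log-rank calculation.

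**2. Count the strata.** 19 × 2 × 2 × 2 = 152; 842/152 = 5.5 participants; 295/152 = 1.9 events. A hospital that recruits only the minimum of 20 (Preconditions for hospital participation) would have 20/8 = 2.5 participants per stratum.

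**3. Simulate.** Each scenario used 2,000 trials with minimization on the four factors, the rates and timing above, and N = 842. Factor proportions, hospital sizes and prognostic effects are assumptions. Uneven hospitals range from 19 to 287 participants. The Monte Carlo standard error is about 0.9 points.

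| Hospitals; % in each binary factor; prognostic effects | Information kept, 152 strata | Power, unstratified | Power, 8 strata | Power, 152 strata |
|---|---|---|---|---|
| Equal; 50/50/50; none | 0.741 | 90.05% | 89.5% | 81.1% |
| Equal; 56/45/50; none | 0.742 | 89.9% | 89.7% | 77.9% |
| Uneven; 56/45/50; none | 0.774 | 90.75% | 89.8% | 81.7% |
| Uneven; 65/40/35; none | 0.786 | 89.9% | 89.5% | 81.9% |
| Uneven; 56/45/50; history HR 2 | 0.771 | 88.25% | 89.35% | 79.8% |
| Uneven; 56/45/50; HRs 1.3, 1.5, 2.5 and hospital SD 0.4 | 0.765 | 88.1% | 89.95% | 82.95% |

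Analytic check, from the information ratio r: power = Φ(3.2415√r − 1.96). For r = 0.741 this is Φ(0.830) = 79.7%; for r = 0.786 it is Φ(0.914) = 82.0%. In a further equal-hospital simulation, 17% of events contributed nothing. Under the null, no version of the test rejected more often than 2.5%.

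**4. Compare the coarser options.** The spread of hospital log-hazards (SD) is an assumption.

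| Hospital SD | Unstratified | 8 strata | Hospital only (19) | 152 strata |
|---|---|---|---|---|
| 0.3, with prognostic factors | 88.8% | 89.3% | 89.0% | 80.6% |
| 0.6, uneven hospitals | 88.5% | 88.8% | 90.6% | 83.3% |
| 0.8, history log-hazard 0.7 | 85.9% | 86.4% | 91.0% | 82.8% |

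**5. The 518 figure.** At 1,036 participants the expected events are 363 and the 152-strata test keeps 0.783 of the information. Power is then Φ(3.2415 × √(363/295 × 0.783) − 1.96), about 89%; simulation gives 89.7%.

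**The case against.** The strongest reply is that the article never writes 152. It says only that stratification is based on the allocation factors, and an analysis plan not shown here could select factors or pool sparse cells. That stands as a condition on the result. It does not remove the point: the article fixes the test and states 90% power beside it, and on the plain reading the two do not agree. This is a figure that does not fit the stated test, not a detail left out.

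A second reply is that 518 per group would carry the 152-strata test to about 90%. The arithmetic is right, but 842 is the total given in both the Abstract and the sample-size section, and it is the size that fits 296 events.

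Third, stratifying on allocation factors is conventional and valid. That is true, and a positive result would stand.

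Fourth, when hospitals differ strongly, the advantage of 8 strata over 152 shrinks to roughly 4–6 points. That also stands, and it is why hospital-only stratification belongs among the options.

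A reader might also infer that the interim and final tests are different statistics, because the Interim analyses section omits the word stratified. The article does not establish this. The phrase may be loose wording, and the section says that the interims address the primary objective, whose test has just been defined. Nor can a size be put on the loss at the interims, since the article gives no event count for them.

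**Conclusion.** The point holds in conditional form. If all four factors are fully crossed without pooling, history has two levels and N is 842, the primary test loses about 21–26% of its information. Its power is then about 78–83%, not 90%, so the chance of missing the target effect roughly doubles, from 10% to about 17–22%. More levels of history would make the loss larger. Prognostic value in the factors does not repay it in any scenario tried. The small cost of two O'Brien-Fleming looks and any loss to follow-up are not included.

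The defect is one of efficiency. It does not threaten type I error or the validity of a significant result. The contrast of 90% with 80% is not fixed either: it depends on hospital sizes and on how far event rates differ between hospitals. The interim wording is an ambiguity to settle, not a demonstrated inconsistency.

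**What to change.** Before unblinding, replace the full cross-classification in the primary test with one of two coarser stratifications:

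- gender, age group and history of attempts (8 strata); or
- hospital alone (19 strata), preferable if event rates are expected to differ strongly between hospitals.

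Put the remaining allocation factors in a supporting Cox model, which the regression already foreseen under Primary analysis can accommodate. If the sponsor keeps all four factors crossed, restate the power at about 80%. In Interim analyses, name the same statistic as in the primary analysis for both looks.

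The cost is two or three sentences in the protocol or analysis plan, with no added participants or data. The downside is that the primary test no longer conditions on every hospital-by-factor cell.
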